### Statistical considerations

The sample size of this study is based on the previously published literature and the corresponding research hypothesis. This study intends to demonstrate that the incidence of strut coverage in the OCT-guided group is higher than that of angiography-guided group at 3-month follow-up (hypothesis 1). The second hypothesis of this study is that the incidence of stent strut coverage in the OCT-guided group at 3 months is similar to the incidence of strut coverage in the angiography-guided group at 6 months (non-inferiority analysis). If the above hypothesis is confirmed then an additional analysis will be performed that aims to demonstrate that the incidence of covered struts is higher at 3 months in the OCT-guided group compared to the rate of strut coverage noted at 6 months in the angiography-guided PCI (hypothesis 3). In order to control for the type I error, the test significance levels of hypothesis 1 and 2 are set at one-sided 0.025. Since hypothesis 3 is a sequential test carried out on the basis of hypothesis 2, the test significance level is set at one-sided 0.05.

The sample size calculation is based on the assumption that each patient will receive on average 1 stents, and that each stent will have a length of 24 mm. OCT analysis will be performed at 0.4/0.6 mm interval and that 7.9 struts in each cross section will be detected. Based on these assumptions, it is estimated that 474 strut results will be obtained from each patient. We estimate that we will need 7,305 strut estimations in each group to prove with 95% power the primary endpoint of the study. Based on the above assumptions, we estimate that 16 patients should be recruited in each group. Considering a 20% drop-off rate, we estimate that 20 patients should be included in each group (Table 4).

**Table 4 tab4:** Parametric assumptions for hypothesis.

	Experimental group coverage	Control group coverage	Non-inferiority margin	Sample size (stent struts)
Hypothesis 1	93.6%	92%	Not applicable	6,781
Hypothesis 2	95%	95%	1.3%	7,305
Hypothesis 3	96.5%	95%	Not applicable	3,912

Continuous variables will be described as means and SDs if they are normally distributed or median and interquartile range in the case of asymmetric data distribution. Categorical variables will be presented as numbers and percentages. Comparisons of numerical variables are conducted with the Student’s *t* test or Mann–Whitney’ *U* test as appropriate, categorical variables and outcomes were compared by using the chi-squared test or Fisher exact test. A statistical package (SPSS 21.0) will be used for analysis. Two-tailed *p* < 0.05 will be considered statistically significant.

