## Methods and analysis

### Study design

The EXPECT study is an investigator-initiated, prospective, multicenter, randomized clinical trial (www.clinicaltrials.gov, NCT04375319). The objective of this study is to evaluate vessel wall healing response over time in NSTE-ACS patients receiving a next-generation DES implantation, and to examine the value of OCT-guided PCI in expediting stent strut coverage, aiming to underscore the potential of a lower duration DAPT in high bleeding risk population.

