There is compelling evidence that strut coverage is a predictor of ST (25). The next-generation DES with thinner struts, safer polymer profiles and improved drug kinetics appear to enable faster endothelialization and have known to reduce the incidence of ST compared to the first generation DES (25). The OCT sub-study of the OPTIMA-C trial revealed favorable strut coverage at 6 months after next-generation DES implantation (23), similarly the FUNCOMBO trial showed almost complete strut coverage of the next-generation DES in patients who presented with STEMI (26). Moreover, a small study reported that in the biodegradable polymer Synergy stent strut coverage was 94.5% at 3 months and 96.6% at 6 months (27) whereas the TARGET All Comers study showed a similar incidence of strut coverage in biodegradable polymer Firehawk and durable polymer XIENCE stent group (99.9 ± 0.3 vs. 100 ± 0.1%, *p* = 0.26) (28). Conversely, the biodegradable polymer BuMA Supreme stent was found to be superior to the XIENCE stent in terms of strut coverage at both 1 month and 2 months in the PIONEER-II OCT trial (29). However, stent implantation in these studies was mostly performed under angiography guidance. The DETECT-OCT (NCT01752894) trial was the first that highlighted the value of OCT imaging in optimizing stent apposition and in this way accelerating strut coverage. In this trial, the percentage of uncovered struts at 3 months was lower in the OCT-guided group (7.5%) than in the angiography-guided group (9.9%; *p* = 0.009) (8). However, the DETECT-OCT trial mainly included patients suffering from stable angina and did not include the group of patients undergoing OCT at a longer follow-up period. This study was designed to provide additional insights as it aims to include NSTE-ACS patients, and include the group of patients that will undergo OCT imaging at 6 months to examine late strut coverage in patients undergoing angiography guided PCI.

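### Testing hypothesis 3 at one-sided 0.05 breaks the claimed type I error control (about 6.8%), and hypothesis 2, with no A3-versus-A6 contrast beside it, cannot by itself show that OCT guidance speeds strut coverage

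*Protocol article*

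**What the plan says.** Study design puts healing over time first: "The objective of this study is to evaluate vessel wall healing response over time in NSTE-ACS patients". It then adds the value of OCT guidance in speeding strut coverage, with shorter DAPT as the wider aim.

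Statistical considerations defines three hypotheses:

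- **H1:** O3 has higher coverage than A3, both at 3 months.
- **H2:** "The second hypothesis of this study is that the incidence of stent strut coverage in the OCT-guided group at 3 months is similar", continuing "to the incidence of strut coverage in the angiography-guided group at 6 months (non-inferiority analysis").
- **H3:** O3 at 3 months has higher coverage than A6 at 6 months, tested only if H2 succeeds.

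On levels it states: "In order to control for the type I error, the test significance levels of hypothesis 1 and 2 are set at one-sided 0.025". It then adds: "Since hypothesis 3 is a sequential test carried out on the basis of hypothesis 2, the test significance level is set at one-sided 0.05".

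Table 4 assumes 93.6% against 92% for H1, 95% against 95% with a 1.3-point margin for H2, and 96.5% against 95% for H3. H2 is not made conditional on H1. Neither the text nor Table 4 contains an A3-versus-A6 comparison, although the Discussion says that the A6 arm is there to examine late coverage after angiography-guided PCI.

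**The concern.** There are three linked problems.

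1. **The level for H3.** A test reached through an earlier test needs no further adjustment, but it inherits that test's level and does not gain a larger one. H2 has 0.025 to pass on. The other 0.025 belongs to H1 and has been spent, whatever H1 shows. Giving H3 0.05 takes the total above the 0.05 that the H1/H2 split implies.

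2. **What H2 can show.** O3 against A6 differs in both guidance and follow-up time. It supports faster healing through OCT only if angiography-guided coverage is still lower at 3 months than at 6. The decision rule does not require any evidence of that.

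3. **The missing contrast.** A3 against A6 is the only randomised comparison of time under the same guidance. It answers the first stated objective and would also check the premise in point 2, yet it is not among the stated comparisons.

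At stake is a positive H2 or H3 being taken as evidence that OCT guidance brings 6-month healing forward to 3 months, in a trial that links its result to DAPT duration.

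**Working it through.** **Inputs** (Statistical considerations and Table 4): the coverage rates above, margin 0.013, levels 0.025, 0.025 and 0.05, power 95%, and 7,305 struts per group. Struts are treated as independent, as the plan does. z(0.025) = 1.960; z(0.05) = 1.645.

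**Reproducing the plan's sample sizes**

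- H2: n = (1.960 + 1.645)² × 2 × 0.95 × 0.05 / 0.013² = 7,305. Matches.
- H1 and H3: n = [z(α)√(2p̄q̄) + 1.645√(p₁q₁ + p₂q₂)]² / δ². H1 (0.936, 0.92, α = 0.025) gives 6,781. H3 (0.965, 0.95, α = 0.05) gives 3,912. Both match, so H3 really was planned at 0.05.
- Patients: (24 / 0.4) × 7.9 = 474 struts each; 7,305 / 474 = 15.4, so 16; 16 / 0.8 = 20. Matches.

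**False superiority claims when O3 = A3 = A6**

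H1 and H3 are then both null. Their statistics share the O3 arm, so their correlation is 0.5.

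- The H2 requirement does not protect H3. The H2 statistic equals the H3 statistic plus 0.013/SE. At 95% coverage SE = √(2 × 0.95 × 0.05 / 7,305) = 0.003606, and 0.013 / 0.003606 = 3.60. Any H3 statistic above 1.645 therefore passes H2.
- Plan as written: 0.025 + 0.05 − P(Z₁ > 1.960, Z₃ > 1.645) = 0.075 − 0.0074 = **0.0676**.
- H3 at 0.025, H1/H2 split kept: 0.025 + 0.025 − 0.0046 = **0.0454**.
- Fixed order H1, H2, H3 at 0.025 each: **0.025**.

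These three figures hold for any correct standard error while 0.013/SE exceeds 1.960 − 1.645 = 0.315. With an assumed intra-patient correlation of 0.10, 16 patients and 474 struts each, the design effect is 1 + 473 × 0.10 = 48.3. SE is then √(2 × 0.0475 × 48.3 / 7,584) = 0.0246, and the ratio is 0.53, so they still hold.

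H1 and H2 alone, both at their null boundaries, also give 0.05 − 0.0046 = 0.0454.

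**What H2 shows when OCT has no effect (O3 = A3)**

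P(H2) = Φ[(O3 − A6 + 0.013)/SE − 1.960], with 7,305 struts per group:

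| O3 = A3 | A6 | Source of the rates | P(H2 declared) |
|---|---|---|---|
| 95% | 95% | assumed plateau | 95.0% |
| 92% | 92% | assumed plateau | 82.5% |
| 94.5% | 95% | cited 3-month rate, plan's A6 | 58% |
| 92% | 95% | Table 4 | about 0 |
| 94.5% | 96.6% | cited pair in the Discussion | below 0.01% |

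At the 95% plateau H2 is declared with H1 not significant in 92.5% of simulated trials. Under within-patient correlation of 0.01 to 0.10 (assumed; the article gives none), the 95.0% falls to about 34% to 8%.

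**Feasibility of A3 versus A6.** With Table 4's 92% and 95%, a one-sided 0.025 test at 95% power needs 1,753 struts per group, well inside 7,305 on the plan's own counting. With the same range of correlation, power is about 88% to 19%.

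**The case against.** **The plateau is not what the plan expects.** This is right. Table 4 has angiography-guided coverage rising from 92% to 95%. The cited biodegradable-polymer study reports that "strut coverage was 94.5% at 3 months and 96.6% at 6 months", a rise of 2.1 points that exceeds the 1.3-point margin. Setting only its 3-month figure against the plan's 95% gives 58%; using the pair gives practically nothing. A reader might infer that H2 is likely to succeed without any OCT effect, and the documents do not support that. What stands is narrower: the interpretation depends on the assumed rise, and no stated comparison checks it.

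**H2 is true under a plateau.** Also right. If all arms have 95% coverage, similarity of O3 and A6 is a correct statement, and it bears on early healing whatever the cause. H1 is the guidance comparison and would be reported beside it. The error would lie in attributing an H2 result to OCT, not in declaring H2.

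**H1 and H2 at 0.025 each are a valid split of one-sided 0.05.** Agreed: their joint error is 4.5%. A reader might infer that two routes to success are themselves uncontrolled; they are not. The excess comes from H3.

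**The time comparison could still be made.** Table 3 measures coverage at 3 and 6 months, and the general two-group tests could be applied to A3 and A6. So it would be too strong to say that the first objective has no analysis. But the article lists its hypotheses and levels, and this contrast is not among them.

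**Conclusion.** The concern holds in this limited form. The type I error statement is wrong as written: with equal coverage in all arms the chance of a false H1 or H3 superiority claim is about 6.8%, against 4.5% with H3 at 0.025 and 2.5% under a fixed order. This assumes a correctly estimated standard error and equal information in the three arms.

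H2 alone establishes similar coverage and not that OCT guidance speeds it. The 95% success rate with no OCT effect is conditional on a plateau at 95% and on independent struts. It illustrates the ambiguity and does not forecast the result.

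No stated hypothesis or comparison isolates time under the same guidance.

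A reader might go further and conclude that H2 must be made conditional on H1. The documents do not require that: the H1/H2 split is acceptable, and a fixed order is one valid alternative.

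**What to change.** 1. **Correct the level for H3.** Either test it at one-sided 0.025 after H2 and keep the H1/H2 split (family error about 4.5%), or test H1, H2 and H3 in that order, each at one-sided 0.025 and each only if the one before succeeds (2.5%). State the intended family-wise level. On the plan's counting the 7,305 struts already exceed the 4,698 that H3 needs at 0.025 with 95% power.
2. **Name the time estimate.** Make A6 minus A3 coverage, with a 95% CI from a patient-level analysis, the estimate for healing over time, and report it beside H2.
3. **Fix the reading of H2.** State that it supports faster healing through OCT only when H1 is also met.

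Items 2 and 3 cost wording and one estimate from data already collected. The fixed order in item 1 has a price: H2 cannot be claimed if H1 fails. With independent struts this is small. At O3 95% and A6 95%, H2 power stays at 95.0% if A3 is 92%, and falls to 94.1% if A3 is 93.4% (the 1.6-point effect planned for H1). With assumed within-patient correlation of 0.05 to 0.10 and A3 at 92%, the chance of claiming H2 falls from about 11% to 7% and from about 8% to 4%. If that loss is unwelcome, the split with H3 at 0.025 avoids it.

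### Hypothesis 3 is tested at one-sided 0.05 behind a gate tested at one-sided 0.025, so the testing sequence does not control the type I error

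*Protocol article*

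**What the plan says.** The Statistical considerations section of the protocol article sets out three hypotheses on strut coverage:

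- **H1:** O3 is superior to A3 (both at 3 months).
- **H2:** O3 at 3 months is non-inferior to A6 at 6 months, margin 1.3 points.
- **H3:** O3 at 3 months is superior to A6 at 6 months.

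On error control it says: "In order to control for the type I error, the test significance levels of hypothesis 1 and 2 are set at one-sided 0.025". H3 follows H2: "If the above hypothesis is confirmed then an additional analysis will be performed". Its level is then raised: "Since hypothesis 3 is a sequential test carried out on the basis of hypothesis 2, the test significance level is set at one-sided 0.05".

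Table 4 gives H1, H2 and H3 their own rows, with 6,781, 7,305 and 3,912 struts per group. The same section closes its paragraph on descriptive and comparative methods with a general criterion: "Two-tailed *p* < 0.05 will be considered statistically significant".

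The article states no familywise level. It does not make H3 conditional on H1, and it does not say that alpha from H1 is passed on.

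**The concern.** In a gated sequence, a later test may reuse the alpha of the test before it, because the later test is reached only when the earlier null has been rejected. It inherits that alpha and gains nothing further. H2 is tested at 0.025, so H3 can inherit 0.025. A level of 0.05 would need a second source, namely the 0.025 spent on H1, and that is available only if H1 has also been rejected. The text makes H3 depend on H2 alone.

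What is at stake is the claim that OCT guidance at 3 months gives better coverage than angiography guidance at 6 months. It concerns the primary endpoint, and the article connects its findings to shorter dual antiplatelet therapy. As planned, this claim would be made at twice the error rate of the hypothesis it follows, inside a scheme presented as controlling the type I error.

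**Working it through.** **Inputs** (Statistical considerations and Table 4): H1 93.6% v 92%; H2 95% v 95%, margin 1.3 points; H3 96.5% v 95%; power 95%; one-sided levels 0.025, 0.025 and 0.05; 1:1:1 allocation. Struts are treated as independent throughout, as the plan does.

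**1. Reproduce Table 4.** For superiority, with p̄ the mean of p₁ and p₂:

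n = [z₁₋α √(2p̄(1−p̄)) + z₀.₉₅ √(p₁(1−p₁) + p₂(1−p₂))]² / (p₁−p₂)²

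- H1, α = 0.025: [1.960 √(2×0.928×0.072) + 1.645 √(0.936×0.064 + 0.92×0.08)]² / 0.016² = 6,780.3, so 6,781. Matches.
- H2, α = 0.025: (1.960 + 1.645)² × 2 × 0.95 × 0.05 / 0.013² = 7,304.7, so 7,305. Matches.
- H3, α = 0.05: [1.645×0.28528 + 1.645×0.28509]² / 0.015² = 3,911.9, so 3,912. Matches.
- H3, α = 0.025: [1.960×0.28528 + 1.645×0.28509]² / 0.015² = 4,697.5, so 4,698. Does not match.

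The one-sided 0.05 was therefore used in the planning; it is not a misprint.

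**2. Does the H2 gate protect H3?** Suppose O3 and A6 both have 95% coverage, so the H3 null holds and non-inferiority is true.

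- Standard error of the difference at 7,305 struts per group: √(2×0.95×0.05/7,305) = 0.00361, or 0.361 points.
- Margin in standard errors: 1.3/0.361 = 3.60.
- H2 passes when Z + 3.60 > 1.960, that is Z > −1.64. H3 passes when Z > 1.645.

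Every result that passes H3 has already passed H2, so the error of H3 is P(Z > 1.645) = 0.050.

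This does not depend on strut independence. The gate starts to bind only when the margin is below 1.960 − 1.645 = 0.315 standard errors. That needs a standard error above 1.3/0.315 ≈ 4.1 points, a design effect of about 131.

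**3. Family error for H1 and H3 when all three arms are equal.** The two test statistics share the O3 arm, so with equal group sizes their correlation is 0.5. By the bivariate normal distribution:

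- H3 at 0.05: P(Z₁ > 1.960 or Z₃ > 1.645) = 0.0676 (upper bound 0.025 + 0.05 = 0.075).
- H3 at 0.025: P(Z₁ > 1.960 or Z₃ > 1.960) = 0.0454 (upper bound 0.05).

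A simulation of 4 million draws that included the H2 gate gave 0.0675 and 0.0453.

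**4. Set against either possible family level.**

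| Family level, one-sided | Where it would come from | Error as planned |
|---|---|---|
| 0.025 | Two-tailed 0.05 | H3 alone reaches 0.050 |
| 0.05 | 0.025 + 0.025 for H1 and H2 | H1 or H3 reaches 0.068 |

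The rule fails on both.

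**5. Power of H3 at 7,305 struts.** Power = Φ[(0.015 √7,305 − z₁₋α × 0.28528)/0.28509]. This is 99.8% at one-sided 0.05 and 99.4% at one-sided 0.025.

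**The case against.** The strongest defence concerns size.

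- **The 6.8% is a worst case.** It needs all three arms equal, whereas Table 4 assumes 92% coverage under angiography guidance at 3 months and 95% at 6 months. If O3 = A3 and A6 is higher, a false H1 or H3 claim becomes less likely: about 3.2% with A6 higher by 0.25 points, 2.6% at 0.5 points and 2.5% at 3 points (strut basis; the first two computed near 95% coverage). If O3 = A6 above A3, H1 is true and only H3 can be false, at 5%.
- **In the planned scenario H1 would nearly always be rejected.** With O3 at 95% and A3 at 92%, the difference is 0.03/√((0.95×0.05 + 0.92×0.08)/7,305) = 7.4 standard errors. H3 at 0.05 then behaves almost as if H1 had passed on its alpha.
- **No family level is stated.** If one-sided 0.05 is meant, the H2–H3 chain taken alone stays within it.
- **The two-tailed criterion may be a general default** that does not apply to the three numbered hypotheses.
- **H3 is an additional analysis** and does not set the sample size.

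The first two points describe likely performance, but familywise control must also hold when the planning assumptions are wrong, including when the arms are equal. The reliance on H1 is also fragile: under an assumed design effect of 10, H1 would be rejected only about 64% of the time (7.4/√10 = 2.33 standard errors). On the third point, the H2–H3 chain does fit within 0.05 by itself, but H1 belongs to the same family and takes the total above it. The fourth point stands in part, so the conflict with the two-tailed criterion is secondary. On the fifth, H3 is a numbered hypothesis on the primary endpoint with its own alpha and its own Table 4 row, so its level has to be right even though it does not drive enrolment.

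**Conclusion.** The level set for H3 is wrong as written. H3 is reached through H2 alone and can carry at most one-sided 0.025, yet the plan gives it 0.05 and Table 4 was computed on that basis. The false-positive rate of H3 is 5% one-sided when O3 and A6 are equal. With all three arms equal, the chance of a false H1 or H3 claim is 6.8%, which exceeds both family levels the text could imply. The 6.8% is the equal-arms case and rests on a correlation of 0.5 through the shared O3 arm; independence would give 7.4% and the upper bound is 7.5%. The 5% for H3 needs only equality of O3 and A6 and a margin of at least 0.315 standard errors.

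A secondary consequence follows if the two-tailed criterion is meant to cover the numbered hypotheses. An H3 statistic between 1.645 and 1.960 would then count as superiority under one rule and as non-significant under the other, with a two-sided 95% interval that includes zero.

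H1 and H2 keep their own individual levels.

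**What to change.** State the familywise level and adopt one of these rules:

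1. **Preferred:** test H3 at one-sided 0.025, read from the same two-sided 95% confidence interval for O3 minus A6 as H2. A lower limit above −1.3 points gives non-inferiority; a lower limit above 0 then gives superiority. With H1 also at 0.025, the family stays within one-sided 0.05.
2. **Alpha passed on from H1:** allow H3 at one-sided 0.05 only when both H1 and H2 have been rejected, and at 0.025 when only H2 has been. The family again stays within one-sided 0.05.
3. **If the family is to be held at one-sided 0.025:** use the fixed sequence H1, then H2, then H3, each at one-sided 0.025.

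Under options 1 and 3, change the H3 entry in Table 4 from 3,912 to 4,698 struts. Say also whether the two-tailed 0.05 criterion applies to the three hypotheses or only to the other comparisons.

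The cost is one or two sentences and at most one table entry. H2's 7,305 struts still determine the sample size, so 20 patients per group is unaffected by this change, and H3 power on the plan's own independent-strut basis falls from 99.8% to 99.4%.

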### Patient enrollment and randomization

Sixty patients with NSTE-ACS (includes unstable angina pectoris and non-ST segment elevation myocardial infarction) from three centers in Huaihai economic zone (Supplementary Table S1) will be enrolled in this trial. The main inclusion and exclusion criteria are listed in Tables 1, 2, respectively.

**Table 1 tab1:** Inclusion criteria.

1. Male or non-pregnant female aged 18–80 years.
2. Clinical diagnosis of acute non-ST segment elevation myocardial infarction.
3. *De novo* coronary artery lesions. Multiple target lesions should be located in different epicardial vessels.
4. Each target lesion should have a length ≤ 40 mm, and diameter between 2.5–4.5 mm by visual assessment.
5. Target lesion with ≥70% diameter stenosis or ≥ 50% diameter stenosis with myocardial ischemia evident by functional assessment.
6. Each patient is allowed to undergo a maximum of three stent implantations, if necessary (except for bailout stent implantation), each target lesion is allowed to be stented with a maximum of two stents.
7. The coronary anatomy is amenable to PCI.
8. Ability to understand the trial purpose, sign informed consent, and have good compliance with medications.

PCI, percutaneous coronary intervention.

**Table 2 tab2:** Exclusion criteria.

1. Acute ST segment elevation myocardial infarction within the past 1 month.
2. Chronic total occlusive lesion, severe left main stem stenosis, lesions with length > 40 mm, bifurcation lesion requiring double stenting, target vessel diameter > 4.5 mm, and vessels unsuitable for OCT imaging such as severely tortuous vessels and vessels with severe dissection, current infection or any active inflammatory diseases.
3. Non interpretable OCT images.
4. Severe calcific lesions that require treatment with debulking techniques.
5. In stent restenosis lesions.
6. Hemodynamic instability such as cardiogenic shock, or left ventricular ejection fraction <40% (by echocardiography or left ventriculography).
7. Renal impairment: eGFR < 60 ml/(min·1.73 m^2^) or serum creatinine>2.5 mg/dL (178 μmol/L), or patients on hemodialysis.
8. Bleeding tendency, history of active peptic ulcer, history of cerebral hemorrhage or subretinal hemorrhage, history of stroke within the past half year, or contraindications for antiplatelet or anticoagulant treatment.
9. Allergy to antithrombotic medications, contrast agent, or Cobalt Chromium.
10. Life expectancy less than 12 months.

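### The sample size treats about 474 struts per patient as independent observations, so the stated 95% power with 16 evaluable patients per arm holds only if within-patient correlation is essentially zero

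*Protocol article*

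**What the plan says.** Under Statistical considerations, the protocol article assumes one 24 mm stent per patient on average, OCT frames every 0.4/0.6 mm and 7.9 struts per cross section. From this "it is estimated that 474 strut results will be obtained from each patient". The requirement is then stated in struts: "We estimate that we will need 7,305 strut estimations in each group to prove with 95% power the primary endpoint of the study". That becomes 16 patients per group, raised to 20 for 20% dropout.

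Table 4 lists, in the order experimental coverage, control coverage, margin and struts:

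- "Hypothesis 1 93.6% 92% Not applicable 6,781"
- "Hypothesis 2 95% 95% 1.3% 7,305"
- "Hypothesis 3 96.5% 95% Not applicable 3,912"

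On significance, "the test significance levels of hypothesis 1 and 2 are set at one-sided 0.025"; for hypothesis 3, "the test significance level is set at one-sided 0.05".

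Patient enrollment and randomization states that patients are allocated 1:1:1 to the three groups. Table 1 adds: "Each patient is allowed to undergo a maximum of three stent implantations". The sample-size paragraph gives no intraclass correlation, design effect or between-patient SD.

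**The concern.** Treatment is assigned to patients, but the calculation counts struts. Struts in one patient share the vessel, the operator, the stent expansion, the plaque and the drug therapy. The article itself names apposition, embedment and plaque composition as determinants of coverage (Introduction) and operator experience as a source of variation (limitations paragraph of the Discussion). Hypothesis 1 also presumes that the way a stent is deployed shifts coverage across its struts. Zero correlation within a patient does not fit that rationale.

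What is at stake is how the trial will be read. It is presented as having 95% power for a 1.6-point difference (hypothesis 1) and a 1.3-point non-inferiority margin (hypothesis 2). If true power is far lower, a failed hypothesis 1 may be taken as no benefit from OCT guidance, and a failed hypothesis 2 as inferiority.

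**Working it through.** **Inputs.** Coverage rates, margin, significance levels, power, 474 struts per patient, and 16 evaluable and 20 enrolled patients per group all come from Statistical considerations and Table 4. The ICC and the patient-level SD are not given there, so the values below are assumptions shown as a range.

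**1. Reproducing the plan's figures, with struts independent and power 95%.**

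- Hypothesis 1: n = [z₀.₉₇₅√(2p̄(1−p̄)) + z₀.₉₅√(p₁(1−p₁)+p₂(1−p₂))]² / (p₁−p₂)², with p₁ = 0.936, p₂ = 0.92 and p̄ = 0.928. Result 6,780.3, rounded up to 6,781.
- Hypothesis 2: n = 2 × 0.95 × 0.05 × (1.960 + 1.645)² / 0.013² = 7,304.7, rounded up to 7,305.
- Hypothesis 3: same formula as hypothesis 1, with 0.965 against 0.95 and z₀.₉₅ for both terms (one-sided 0.05). Result 3,911.9, rounded up to 3,912.
- Struts per patient: 24/0.4 × 7.9 = 474.
- Patients: 7,305/474 = 15.4, rounded up to 16; 16/0.8 = 20.

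Every figure matches, so the design effect used was exactly 1. (The 474 uses only the 0.4 mm interval. At 0.6 mm, 24/0.6 × 7.9 = 316 struts and 7,305/316 = 23.1, so 24 patients would be needed even under independence.)

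**2. Allowing for clustering.** Design effect = 1 + (474 − 1) × ICC. Effective struts per arm = 16 × 474 / design effect = 7,584 / design effect.

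| Assumed ICC | Design effect | Effective struts | Power H1 | Power H2 |
|---|---|---|---|---|
| 0 | 1 | 7,584 | 97% | 96% |
| 0.001 | 1.5 | 5,149 | 88% | 86% |
| 0.002 | 1.9 | 3,897 | 78% | 75% |
| 0.005 | 3.4 | 2,254 | 55% | 52% |
| 0.01 | 5.7 | 1,324 | 36% | 34% |
| 0.02 | 10.5 | 725 | 22% | 21% |
| 0.05 | 24.7 | 308 | 12% | 11% |

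The slack is 7,584/7,305 = 1.038. Hypothesis 2 therefore keeps 95% power only while 473 × ICC ≤ 0.038, that is ICC ≤ 0.00008.

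**3. The same check per patient.** Take each patient's coverage percentage as one observation, 16 per arm, two-sample t test, one-sided 0.025, noncentral t with 30 degrees of freedom.

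| Assumed SD of patient percentages (points) | Power H1 (1.6 points) | Power H2 (1.3 points) | Difference detectable with 80% power (points) |
|---|---|---|---|
| 2 | 59% | 43% | 2.0 |
| 3 | 31% | 22% | 3.1 |
| 5 | 14% | 11% | 5.1 |

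95% power needs an SD of at most about 1.2 points for hypothesis 1 and about 1.0 point for hypothesis 2. Sampling of 474 struts alone, with no true difference between patients, gives √(0.95 × 0.05/474) = 1.0 point at 95% coverage, and 1.1 to 1.2 points at the rates of hypothesis 1. The stated power thus leaves practically no room for real variation between patients.

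**The case against.** - **The size depends on an ICC that the document does not give.** This stands. At very small values the loss is moderate: 88% and 86% at ICC 0.001. The exact power is unknown. What is known is that 95% requires a correlation of practically zero.
- **The article does cite one spread of coverage**, 99.9 ± 0.3% against 100 ± 0.1% in the Discussion. Its unit is not stated, and it sits at the ceiling rather than at 92% to 96.5%, so it transfers poorly. Nor does it support independence. Read as a patient-level SD with 474 struts, binomial noise would be √(0.999 × 0.001/474) = 0.15 points. An SD of 0.3 then means a design effect of about 4 and an ICC near 0.007.
- **An analysis plan not shown may use a clustered model.** That could protect the type I error. It cannot restore power that the article itself states and that the number of patients does not support.
- **Low power is only one of two possible harms.** This is right. If struts were tested naively as independent, the problem would be false positives: a nominal one-sided 0.025 test would have a true error of 1 − Φ(1.96/√5.73) = 0.21 at ICC 0.01 and 0.35 at ICC 0.05. The article's list of tests does not settle which case applies.
- **The three-stent allowance adds little.** Agreed; no figure above depends on it.
- **Patient percentages near 100% are skewed**, so the t-based figures are approximate. This is fair, but it does not change the conclusion.

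**Conclusion.** The concern holds. The arithmetic is right for independent struts, but the unit is wrong for a trial that randomises patients. That struts were taken as independent follows from the article's own numbers and needs no outside assumption. The size of the loss does rest on an assumed ICC or SD. Hypothesis 2 loses its 95% at an ICC of about 0.0001, power for hypotheses 1 and 2 is roughly halved at 0.005, and it is about one third at 0.01. This must be corrected, because it is the stated justification for the size of the primary comparison.

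**What to change.** Withdraw the 95% power statement. Rewrite the sample-size paragraph and Table 4 per patient: give an assumed between-patient SD (or ICC) with its source and a range, and report the power or detectable difference for 16 evaluable (20 randomised) patients per arm. Possible wording: with 16 evaluable patients per arm and a one-sided 0.025 test, the trial has 80% power to detect a difference in mean patient-level coverage of 2.0, 3.1 or 5.1 percentage points if the between-patient SD is 2, 3 or 5 points.

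Unless the SD can be shown to be about 1 point (up to about 1.2 for hypothesis 1), it would be sensible to present hypotheses 1 to 3 as exploratory, or to rest the conclusions on estimates with 95% confidence intervals. That label is the sponsor's choice; correcting the power statement is not optional.

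The 60 patients can stay. The cost is rewording and a much less favourable stated power, with no extra patients or procedures.
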